### Think-aloud study

A qualitative think-aloud study^33^ including a short semistructured interview was conducted following the development of the initial version of the intervention with the aim to understand participants’ first impressions and attitudes towards the intervention, and to collate feedback that could be used to make improvements. Details and outcomes of this study are provided in online supplementary material 3.

10.1136/bmjopen-2019-030607.supp3Supplementary data

### Analyses of the RCT data

#### Quantitative analyses

A full and detailed statistical analysis plan will be written prior to trial closure. In brief, the data analysis will be performed on an intention-to-treat (ITT) basis to provide an unbiased estimate of the treatment effect.^56^ Per-protocol analyses will also be performed (comprising those correctly randomised, without protocol violations, and providing complete data on the primary outcome measure). Sweetman and Doig^57^ have identified five types of protocol violations, namely violations in (1) enrolment (ie, failure to correctly apply eligibility criteria resulting in the enrolment of an inappropriate participant); (2) randomisation (ie, violation of intended randomisation sequence); (3) study intervention (ie, dosing, timing or delivery errors attributable to members of the research team); (4) patient compliance (ie, participants failing to comply with the trial protocol or other requirements of participation in the trial, such as skipping scheduled appointments or sessions); and (5) data collection (ie, a failure by the research team to comply with prespecific trial guidelines for data collection and/or outcome evaluation due to avoidable reasons). Any such violations will be clearly reported.

Analyses undertaken will include the following:

The primary analysis on pain interference will use the initial 2×2×2 structure comprising stage (baseline, 10 weeks), randomised treatment (attentional bias modification training (ABMT), placebo) and randomised number of sessions (10, 18). This comparison will be extended to compare 10AMG and 10PTG after 10 sessions, and to compare 18AMG and 18PTG after 10 sessions.An analysis of pain interference will use the 2×2×3 structure comprising randomised treatment (ABMT, placebo), randomised number of sessions (10, 18) and stage (baseline, endline, follow-up).An assessment of change in pain interference, both within and between groups, for 18AMG and 18PTG, between the end of session 10 and endline.The four randomised arms compared against one another on pain interference at each of baseline, after session 10, endline and follow-up.An age (16–24, 25–60) subgroup analysis using an age subgroup by treatment effect interaction. These analyses will be an extension of (1), (2) and (3) to incorporate age as a subgroup factor.

The same analyses would apply to the secondary outcome measures. The data will be represented descriptively and graphically by arm, and by treatment and age, and standardised effect sizes reported.

Linear mixed model with random intercepts will be used to analyse the data with, as appropriate, treatment (ABMT, placebo), number of sessions (10, 18) and assessment stage as fixed factors. This approach avoids listwise deletion which would apply in a repeated measures analysis of variance approach. The linear mixed modelling approach uses all of the available data and adheres to ITT. As a secondary analysis we will used multiple imputation chained equations to impute outcome data^58 59^ and use these imputed data sets in the linear mixed model. Pairwise comparisons will follow the same procedure. An assessment of the sensitivity of findings to missing data mechanisms will be undertaken.^60 61^ Specifically, we will use the strategy discussed by Morris and colleagues^61^ whereby multiply imputed values are altered by a randomised group-dependent value prior to analysis. We will run this sensitivity analysis over a factorial arrangement of group-dependent values constraining any altered imputed values to be in the valid response range. The instance of the group-dependent values both being equal to zero will correspond to multiple imputation under missing at random (MAR), and non-zero values would reflect deviations away from this assumption. The analysis plan would apply to the primary outcome measure and secondary outcome measures.

Similar to previous studies,^25 27^ the Reliable Change Index^62^ will be used to assess primary and secondary outcome measures for clinically significant changes. Here, a clinically significant result is a post-treatment score falling outside 2 SD of the mean population of interest (in this study, 2 SD outside pretreatment means). In contrast to tests of statistical significance comparing group means, tests of clinical significance explore effects of treatment on the individual.^63^

For visual-probe data, and as per previous research,^19 27^ practice and incorrect trials will be removed prior to analyses. Box and whisker plots for overall data will be used to reveal overall outliers, which will be removed. Following this, mean response times will be computed for each participant, with any response >3 SD from their individual mean also removed as outliers. This process ensures extremely quick or slow responses do not unduly bias the results, which are typically removed when cleaning and screening visual-probe data in pain-related research (eg, refs 18 64–67). An attentional bias index will then be computed for each stimulus and presentation time condition using the following equation: (TuPl−TlPl)+(TlPu−TuPu)/2. Here T is the threatening stimulus, P is the probe, u is the upper position and l is the lower position. The attention capturing quality of threatening stimuli is measured by subtracting the mean probe classification time for congruent trials from the mean probe classification time of incongruent trials.^21^

Split-half reliability will be computed via a bootstrap procedure, by randomly splitting the total number of trials in two halves, such that each half has the same number of congruent and incongruent trials. Attentional bias scores will be computed for each half and the correlation between them calculated across participants. This procedure will be repeated 100 times, and an average split-half correlation computed.

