### Study design and setting

The study is a double-blind RCT with four arms exploring the efficacy of online ABM training versus a placebo training condition theorised to offer no specific therapeutic benefits. The choice of comparator was selected as placebo training closely mimics ABM training, and is frequently used as a comparator in ABM studies (eg, refs 25 26 34 35). The study will take place in a location of the participant’s choice (which we anticipate will typically be their home) and will be accessed via personal computer connected to the internet.

The study design has a 2×2×3 experimental structure, with multiple non-commensurate dependent variables measuring pain intensity and interference, emotional functioning, and pain-related disability. Treatment is a two-level factor (ABM, placebo), and the number of sessions is a two-level factor (10 sessions, 18 sessions), with measures recorded at three points in time (baseline, endline and 6-month follow-up). Measures in the 18-session groups (18AMG and 18PTG) will also be taken after session 10.

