### Procedure

Interested individuals will contact the researchers on the details provided in study advertisements and will be assessed against the inclusion and exclusion criteria via telephone interview. If eligible, they will receive a copy of the participant information sheet detailing the requirements and procedure of the study, along with a link to the study website which provides further details on ABM and the research team. If the individual consents to take part, they will be required to create an online ABM account. During registration, participants will select their preferred days for training, which will be either (1) Monday/Thursday or (2) Tuesday/Friday.

Session 1 is the baseline session, and includes the first assessment visual-probe task measuring attentional biases prior to beginning the intervention, along with the questionnaire battery assessing the primary and secondary outcome measures. Randomisation will take place following session 1, where participants will be informed of the length of their training (ie, 4 or 8 weeks). Participants randomised to either of the 10-session conditions will complete four pictorial and four linguistic training sessions, while those randomised to either of the 18-session conditions will complete eight pictorial and eight linguistic training sessions (baseline and endline assessment sessions comprise the remainder of the 10/18 sessions). Participants’ attentional biases will be reassessed at endline (ie, during the final session 10/18) using the same assessment version of the visual-probe task (ie, featuring the same stimuli) used at baseline and the same questionnaire battery. Participants randomised to either of the 18-session conditions will also have their attentional biases reassessed in session 10 after their training session.

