### Outcome measures

The primary outcome measure of pain interference will be assessed by the Brief Pain Inventory-Short Form.^37^ Pain interference will be scored as the mean of seven interference items (ie, general activity, walking, work, mood, enjoyment of life, relations with others and sleep). Following guidance in the Brief Pain Inventory User Guide^49^ and also Initiative on Methods, Measurement, and Pain Assessment in Clinical Trials (IMMPACT) recommendations for assessing pain in clinical trials,^50^ we will include individual assessments of ‘worst’, ‘least’, ‘average’ and ‘now’ (ie, current) pain intensity as secondary outcome measures. Additional secondary outcome measures of state and trait anxiety will be assessed by the State Trait Anxiety Inventory,^51^ depression by the Hospital Anxiety and Depression Scale,^52^ pain-related fear by the Fear of Pain Questionnaire III,^53^ sleeping impairment by the Medical Outcomes Study-Sleep Scale,^54^ and engagement to and satisfaction with the online visual-probe training task by the Satisfaction with the Online Training questionnaire (SOT)^55^ and the Engagement with the Online Training questionnaire (EOT). A demographic questionnaire developed by the researchers will be used at baseline to collect information on participants’ age, gender, ethnicity, socioeconomic status, place of residence and pain characteristics. Aside from the SOT and EOT, questionnaires in the 10-session groups (10AMG and 10PTG) will be administered to participants at baseline, after 10 sessions and at 6-month follow-up. In the 18-session groups (18AMG and 18PTG), questionnaires will be administered to participants at baseline, after 10 sessions, after 18 sessions and at 6-month follow-up. At endline for each participant, we will also assess whether the participant and researchers became aware at any point prior to endline which group they had been allocated to. Full details on each outcome measure are provided in online supplementary material 2.

10.1136/bmjopen-2019-030607.supp2Supplementary data

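### Analysis (2), the non-primary model behind the endline and dose hypotheses, has no level for the session-10 score of the 18-session arms, so participants who stop between sessions 10 and 18 enter it without that score

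*Protocol article*

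**What the plan says.** All references are to the protocol article.

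- **Stages of the model.** Under Quantitative analyses, analysis (2) for pain interference crosses treatment with "randomised number of sessions (10, 18) and stage (baseline, endline, follow-up"). Study design and setting describes the same structure, with "measures recorded at three points in time (baseline, endline and 6-month follow-up").
- **Meaning of endline.** Under Procedure, attentional bias and the questionnaires are "reassessed at endline (ie, during the final session 10/18"). Endline is thus session 10 in the 10-session arms and session 18 in the 18-session arms.
- **The extra measurement.** Study design and setting adds: "Measures in the 18-session groups (18AMG and 18PTG) will also be taken after session 10". Outcome measures confirms this for the 18-session arms: "questionnaires will be administered to participants at baseline, after 10 sessions, after 18 sessions and at 6-month follow-up".
- **The model.** The article specifies: "Linear mixed model with random intercepts will be used to analyse the data with, as appropriate". Its fixed factors are treatment arm, session count and stage.
- **The use of data.** The stated advantage of the model is this: "This approach avoids listwise deletion which would apply in a repeated measures analysis of variance approach". The article then makes the broader claim at issue here: "The linear mixed modelling approach uses all of the available data and adheres to ITT".
- **Other uses of the session-10 score.** It is the outcome of analysis (1), which is the primary and powered analysis, the starting point of analysis (3), and one of the listed stages of analysis (4).

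**The concern.** The Introduction places the efficacy hypotheses at endline and adds that 18 sessions should do better than 10. Analysis (1) cannot test dose, because at session 10 all arms have had the same number of sessions. Analysis (3) uses the 18-session arms only, and analysis (4) compares arms stage by stage without naming an interaction. Analysis (2) is therefore the only listed factorial model with treatment, number of sessions and endline together. It is also extended to the age subgroups and the secondary outcomes.

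An 18-session participant who stops after session 10 has a post-baseline score that this model does not see. Missing at random must then hold given baseline (and follow-up, if observed), without regard to how the participant was doing after session 10. If poor response so far drives stopping, and does so differently under ABM and placebo, the 18-session treatment effect at endline is biased. The treatment-by-sessions interaction is biased by the same amount, and the treatment effect averaged over the two session lengths by half of it. Only the 18-session arms have this window.

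**Working it through.** **Inputs from the protocol (Randomisation and sample size).** Correlation 0.7, stated for baseline with session 10; 20 per arm needed; 20% allowance for loss. The recruitment figure reproduces: 4 × 20 = 80, and 80/(1 − 0.2) = 100, or 25 per arm. It concerns session 10 and is not touched by this point.

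**Assumptions, not in the documents.** Unit SDs. Correlation 0.7 between all stages, which a random-intercept model implies once it is 0.7 for one pair. A fraction r = 0.20 of each 18-session arm stops after session 10. Stopping depends on change from baseline to session 10, with log-odds 0.5, 1.0 or 1.5 per outcome SD.

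**Precision, stoppers also missing follow-up.** Of 25 per arm, 20 complete.

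- Three stages: endline is predicted from baseline with slope 0.7 and residual variance 1 − 0.49 = 0.51. Variance of the arm's change = 0.51/20 + (1 − 0.7)²/25 = 0.0255 + 0.0036 = 0.0291. SE of the difference = √(2 × 0.0291) = 0.241.
- With session 10: slope on each of baseline and session 10 is 0.7/1.7 = 0.412, and residual variance is 1 − 2(0.49)/1.7 = 0.4235. Variance = 0.4235/20 + (0.412² + 0.588² − 2 × 0.412 × 0.588 × 0.7)/25 = 0.02118 + 0.00706 = 0.02824. SE = √(2 × 0.02824) = 0.238.
- Variance ratio 0.02824/0.0291 = 0.970, a gain of 3%. Over 10% to 40% stopping the gain is 1.5% to 6.1%.

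**Bias.** Let X be the stoppers' mean excess in baseline-adjusted session-10 score over their arm, in SD (higher is worse). Completers are then better than the arm by r/(1 − r) × X = 0.25X.

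- Stoppers miss follow-up: the three-stage model shifts the arm's endline mean by 0.412 × 0.25X = 0.103X.
- Stoppers give follow-up: the multiplier 0.412 becomes (0.7/2.4) × (1 − 0.412²) = 0.242, so the bias is 1 − 0.242/0.412 = 41% lower.
- Setting the logistic intercept to give 20% stopping, numerical integration gives X = 0.199, 0.373 and 0.508 for log-odds 0.5, 1.0 and 1.5.

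Bias in ABM v placebo at endline, 18-session arms, in SD (follow-up missed / follow-up given):

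| Log-odds per SD | Same in both arms | ABM only, placebo at random | Opposite directions |
|---|---|---|---|
| 0.5 | 0 / 0 | 0.021 / 0.012 | 0.041 / 0.024 |
| 1.0 | 0 / 0 | 0.038 / 0.023 | 0.077 / 0.045 |
| 1.5 | 0 / 0 | 0.052 / 0.031 | 0.105 / 0.062 |

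Large-sample simulation of the same model agrees to within about 0.002. With session 10 in the model the bias is zero in every cell. That is by construction, since stopping was made to depend only on scores the model then contains. The largest entry is 0.105/0.241 = 0.44 of one SE.

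**The case against.** The case on the other side is substantial, and most of it stands.

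- **The score is not thrown away.** A reader might infer that the plan discards it. It does not: analyses (1), (3) and (4) use it, and analysis (4) also compares the arms at endline. The article does not say whether (4) is one joint model or several, so nothing shows that (4) leaves session 10 out of its model.
- **The data-use sentence is not a flat contradiction.** It follows directly on the contrast with listwise deletion and can be read as saying that incomplete cases are kept. That is true of analysis (2) at its own stages. What remains is that avoiding listwise deletion is not the same as using every score collected.
- **Missing data are handled further.** The plan adds multiple imputation and a sensitivity analysis that shifts imputed values by arm, which probes arm-specific departures from missing at random. A reader might infer that the imputation ignores session 10. The article is silent on its predictors, and that may be left to the analysis plan.
- **The size is assumed.** In a double-blind trial whose placebo closely mimics the active task, similar stopping in both arms is the natural starting point, and the bias is then zero. The top of the range needs non-responders to leave ABM while responders leave placebo, which nothing in the documents suggests.

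None of this gives the session-10 score a place in analysis (2) itself. The stage levels are stated there, so this is a fixed rule and not a detail still to come.

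**Conclusion.** The point holds in a limited form. As written, analysis (2) omits the session-10 score of the 18-session arms, and those who stop between sessions 10 and 18 contribute baseline only, plus follow-up if given.

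The consequence is conditional. At an assumed 20% stopping and correlation 0.7, the 18-session ABM v placebo endline effect is unbiased if stopping works alike in both arms. If it differs by arm, the bias is about 0.02 to 0.11 SD when follow-up is also missed and about 0.01 to 0.06 SD when it is given. The gain in precision is negligible, so the benefit is protection against arm-differential stopping in a non-primary analysis.

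A reader might go further and infer that the trial's main result is biased. The documents do not support that: the primary and powered comparison is at session 10, and no stopping rate or mechanism is given for later sessions. This is a change to consider.

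**What to change.** Fit analysis (2) as an arm-by-visit mixed model with visits baseline, session 10, session 18 (18-session arms only) and 6-month follow-up. Obtain the treatment, dose and interaction effects at endline as contrasts, taking session 10 as endline for the 10-session arms and session 18 for the 18-session arms. If the three-stage model is kept, limit the data-use sentence to the stages in each model.

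The cost is wording in the analysis plan, which the article says is still to be written. No new data are needed. The small downside is that the balanced 2×2×3 factorial becomes an unbalanced cell-means model, whose dose and interaction contrasts must be written out.

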Our previous lab-based, proof-of-concept ABM intervention found reductions in pain intensity and pain interference from pre-ABM to post-ABM were associated with large effect sizes,^27^ although differences in methodology including delivery (online vs lab-based) and number of sessions warrant a more conservative estimate. On this basis, the study will recruit a minimum of 100 with 1:1:1:1 randomisation. This study is powered primarily to establish treatment efficacy for the primary outcome variable of pain interference by considering baseline and measures after session 10 between those randomised to an attentional modification arm and those randomised to a placebo arm. Randomisation should ensure baseline comparability on measures between these two groups, and a difference in beneficial outcomes between these groups will be modelled using a linear mixed model. For an assumed correlation of 0.7 between baseline and end of session 10 measures, a total of 40 per group (ie, 20 per randomised arm) would be needed to detect small to moderate standardised intervention differences (Cohen’s *d*=0.25) with at least 80% power (alpha=0.05, two-sided). The recruitment strategy includes a 20% oversampling to mitigate a loss of power from loss to follow-up.

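### The primary mixed model leaves baseline means free and gives up 15% of its information; in the three-stage analysis, random intercepts may misstate standard errors if correlations decay over time

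*Protocol article*

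**What the plan says.** Under Quantitative analyses, the protocol article commits to a model: "Linear mixed model with random intercepts will be used to analyse the data". The fixed part is listed, as appropriate, as "treatment (ABMT, placebo), number of sessions (10, 18) and assessment stage as fixed factors". No baseline covariate, equal-baseline constraint, other covariance structure or robust standard error is named.

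Baseline is an outcome level in both main analyses. For the primary analysis: "The primary analysis on pain interference will use the initial 2×2×2 structure comprising stage (baseline, 10 weeks"; the sample-size section describes the second stage as the measure after session 10. The second analysis crosses treatment with "randomised number of sessions (10, 18) and stage (baseline, endline, follow-up". A further item has "The four randomised arms compared against one another on pain interference at each of baseline, after session 10, endline and follow-up", so arm means at baseline are themselves estimated and compared. The same analyses apply to the secondary outcomes.

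Under Randomisation and sample size, the article says "Randomisation should ensure baseline comparability on measures between these two groups", and gives its only correlation: "For an assumed correlation of 0.7 between baseline and end of session 10 measures". It gives none involving the 6-month visit.

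**The concern.** Two features of this model deserve attention, and they differ in kind.

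First, when each arm has its own baseline mean, the treatment-by-stage term in a two-stage model is the difference between groups in raw change. Randomisation makes the true baseline means equal, as the article itself notes, but the model does not use that fact. The result is an interval wider than the same data would allow.

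Second, random intercepts alone impose one variance and one correlation on every pair of stages. With three stages, baseline must correlate with the 6-month follow-up as strongly as with endline, although endline closes a 4-week or 8-week course and follow-up comes six months after the last session. If the correlation falls with time, the pooled residual variance is too small for the baseline-to-follow-up contrast and too large for baseline-to-endline. Follow-up findings would then carry excess false positives, and endline findings would lose power.

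**Working it through.** **Inputs from the article:** r=0.7 (baseline to session 10), d=0.25, 40 per treatment group, 80% power, two-sided alpha 0.05, 20% oversampling, 100 recruited. **Assumed here:** equal variances across stages, and the three-stage correlation sets listed below.

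**The plan's own sample size.** With variance factor v, n per group = 2v(1.96+0.842)²/d².
- Change score, v=2(1−r)=0.60: 2×0.60×7.85/0.0625, giving 151 per group.
- Baseline-adjusted, v=1−r²=0.51: 2×0.51×7.85/0.0625, giving 129 per group.

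The stated 40 per group is not reproduced at a between-group d of 0.25. It is reproduced only if 0.125 is used as the interaction effect size f (78 in total). That corresponds to a difference in change of d=0.5, for which 2×0.60×7.85/0.25 gives 38 per group. The step to 100 does reproduce: 80/(1−0.20)=100.

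**Information lost in the primary contrast.** The ratio is 0.51/0.60=0.85, a loss of 15%; equivalently 0.60/0.51=1.18, worth about 18% more participants. With 40 per group:

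| Analysis | SE = √(2v/40) | Power at d=0.25 | Detectable d at 80% power |
|---|---|---|---|
| Free baseline (change) | 0.173 | 30% | 0.49 |
| Baseline-adjusted | 0.160 | 35% | 0.45 |

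Power is Φ(0.25/SE−1.96); detectable d is 2.80×SE.

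**Validity of the primary standard error.** Two stages have only one correlation, so a random intercept is adequate for the free-baseline contrast. Fitting the model to 300 simulated trials gave a mean model SE of 0.173 against an empirical 0.169. With unequal variances (SD ratio 1.2) it gave 0.194 against 0.193.

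**Three-stage analysis.** With complete data, the random-intercept model takes the variance of any change as 2(1−r̄), where r̄ is the mean of the three correlations; the true value for a given pair is 2(1−r). The SE ratio (model/true) is √((1−r̄)/(1−r)), and type I error is 2(1−Φ(1.96×ratio)). Correlations are in the order baseline-endline, baseline-follow-up, endline-follow-up:

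| Correlations | r̄ | Follow-up: SE ratio, type I error | Endline: SE ratio, type I error |
|---|---|---|---|
| 0.7/0.7/0.7 | 0.70 | 1.000, 5.0% | 1.000, 5.0% |
| 0.7/0.6/0.65 | 0.65 | 0.935, 6.7% | 1.080, 3.4% |
| 0.7/0.5/0.6 | 0.60 | 0.894, 8.0% | 1.155, 2.4% |

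For the last row, 20,000 simulated trials with 40 per group gave 8.1% and 2.3%.

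**The case against.** A reader might infer that a random-intercept model gives wrong standard errors throughout, including in the primary analysis. The documents do not support that. The primary analysis has two stages and its standard error is valid. In the three-stage analysis the errors are wrong only if correlations or variances differ between stages. The article gives no figures on this, and equal correlations of 0.7 produce no error at all. Decay is plausible given the spacing of visits, but it is an assumption.

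It can also be said that a difference in change is unbiased under randomisation, so the baseline point is about efficiency only. That is right, and it is put no higher here. Nor should the 15% be read as a remedy for low power: the move from about 30% to 35% leaves the sample-size problem where it was.

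Finally, the article describes its analysis in brief, lists the fixed factors as appropriate and promises a full statistical analysis plan. A random intercept does not by itself rule out a structured residual covariance, and the free-baseline contrast is inferred from the factor structure. This leaves some room. But the article does name a specific random-effects structure, makes baseline a level of the outcome factor and compares arms at baseline, while naming no adjustment. The natural reading is the model examined here, and an improvement to a stated model is not a complaint about missing detail.

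**Conclusion.** The point holds in two limited parts.

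- **Primary analysis:** valid but inefficient. On the natural reading of the model, with the article's r=0.7 and equal variances, 15% of the information is given up. The gain from recovering it is real but modest.
- **Three-stage analysis (not primary):** a conditional risk. Follow-up type I error ranges from 5.0% with no decay to about 8.0% under 0.7/0.5/0.6, and endline from 5.0% down to about 2.4%. The size rests wholly on assumed correlations.

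Both are worth settling in the statistical analysis plan, because the remedies use data already being collected and remain valid if the correlations turn out equal.

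**What to change.** For the primary and secondary outcomes, constrain the randomised arms to a common baseline mean, or regress the session-10 score on baseline score, treatment and number of sessions. The common-mean form keeps participants who have only a baseline score, in line with the article's wish to use all available data; pair it with an unstructured two-stage covariance so that it does not rely on equal variances. The planned comparison of arms at baseline then becomes descriptive.

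For the three-stage analysis, replace the random-intercept structure with an unstructured covariance across baseline, endline and follow-up, with Kenward-Roger degrees of freedom. This needs six covariance parameters (three variances, three correlations) instead of two. It should stay at three stages: session 10 is the endline in the 10-session arms, so a four-stage unstructured matrix would be fully informed only by the 18-session arms, about 50 of the 100 recruited and about 40 after the planned 20% loss.

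The cost is plan wording and a few more covariance parameters. The sample-size justification needs separate attention.
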